#### Potential serious adverse events (SAEs) not directly related to the trial and adverse events (AEs)

Children’s schooling or parent/guardians’ work is adversely affected (e.g. due to time spent in therapy or assessments encroaching on school or homework time).One or more aspect of the therapy or assessment procedure induces unacceptable levels of distress for either the participant, their parent/guardian, or the therapist.It becomes apparent that one or more of the exclusion criteria is met (or inclusion criteria not met) by the participant. [NB. This will be logged but the participant remains in treatment as long as clinically appropriate and retained in the intent to treat sample.]A sustained and significant increase in detrimental behaviours (e.g. safety-seeking behaviours) as determined by any of the outcome measures collected throughout the study.The emergence of new detrimental behaviours (e.g. self-harm).Drop-out of treatment/request to change therapist (all routinely monitored for the presence of AEs).A complaint is received from a participant, their parent/guardian, or the therapist referring to an actual or perceived adverse event as defined above.

The window for reporting SAEs and AEs will be:(i)During the treatment phase based on therapist report(ii)Up to the end of study based on parent report (i.e. up to the 26-week assessment or qualitative interview, whichever is later).

The 14-week and 26-week assessments will include questionnaires to monitor participants’ functioning and quality of life; therefore, information on some of the potential adverse events identified in this document will be routinely collected. Therapists will also be asked to indicate the presence of an SAE or AE that arises during the course of treatment. Further investigation will be made by the clinical team and the PI and the SAE/AE procedures will be followed where applicable. Specifically, the clinical team and the PI will assess the frequency and severity of the adverse event(s) and determine whether the participant should be withdrawn from the trial. The decision of the clinical team will be followed in the event that a consensus is not reached. Participants will also be given the opportunity to report adverse events anonymously after the parent and child complete questionnaires at 14 and 26 weeks and in person (remotely) after the qualitative interviews (for the parents). The research team will regularly review responses to identify any responses that indicate the presence of an adverse event and will report summaries of these responses to the Trial Steering Committee for review.

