Therapist Economic Logs (Supervision Logs and Treatment Logs): We will collect economic logs from therapists during the treatment phase (up to 26 weeks if applicable; in the C-TAU arm where there is no set end point to the treatment). Therapists in both trial arms will be asked to complete an economic log throughout treatment, to record all staff-time spent on treatment-related activities (e.g. training and supervision, preparation of sessions, administration, phone contact with parent, video-contact with child whenever applicable).

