#### Reporting procedures for adverse events/serious adverse events

All AEs and SAEs will be recorded, logged, and monitored by the PI and TMG. If an AE is reported more than once for a participant, or more than three times during the study, it will be treated as an SAE.

A serious adverse event (SAE) occurring to a participant will be reported to the REC that gave the favourable opinion of the study where in the opinion of the Chief Investigator the event was ‘related’ (resulted from administration of any of the research procedures) and ‘unexpected’ in relation to those procedures. Reports of related and unexpected SAEs will be submitted within 15 working days of the Chief Investigator becoming aware of the event, using the HRA report of serious adverse event form.

In the event that a complaint is received from a participating parent or child, the therapists, or their managers, the CI will attempt to resolve the issue as far as is possible. If this is not possible, and the issue remains unacceptable to participants, formal complaints will be logged and dealt with by the sponsor’s representative in liaison with the CI. Those indicating an AE or SAE will be logged accordingly.

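### The second adverse-event list puts therapy-attributed events under a heading whose only serious category is unrelated to the trial, and includes trial-conduct events that the escalation rule could turn into SAEs

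*Protocol article*

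**What the plan says.** Four sections of the protocol article, all under the adverse event heading {22}, bear on this point.

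- **Definition of serious adverse events.** An SAE is an untoward medical occurrence that meets one of the listed outcomes, or an important medical event that may need intervention to prevent one. The section then announces a non-exhaustive list of potential SAEs and AEs and expects SAE risk to be very low.
- **The first list (potential SAEs to parent or child).** It carries no statement about relatedness.
- **The second list.** It is headed "Potential serious adverse events (SAEs) not directly related to the trial and adverse events (AEs" and does not say which items belong to which half of the heading. One item is "One or more aspect of the therapy or assessment procedure induces unacceptable levels of distress for either the participant, their parent/guardian, or the therapist". Another is an adverse effect on schooling or parental work, with the example "due to time spent in therapy or assessments encroaching on school or homework time". A third is "It becomes apparent that one or more of the exclusion criteria is met (or inclusion criteria not met) by the participant", with the note "This will be logged but the participant remains in treatment as long as clinically appropriate and retained in the intent to treat sample". Drop-out and requests to change therapist also appear, with a bracket saying that they are routinely monitored for AEs.
- **Reporting procedures.** All AEs and SAEs are logged. An AE reported more than once for one participant, or more than three times in the study, is treated as an SAE. An SAE goes to the Research Ethics Committee (REC) when the Chief Investigator considers it unexpected and related, where related means that it "resulted from administration of any of the research procedures".

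**The concern.** Two things in the second list do not fit the sections around it.

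First, its heading names only one kind of serious event, the kind not directly related to the trial. Yet distress brought on by therapy or assessment, and schooling lost to therapy time, are consequences of the trial's procedures as the items themselves are worded. If such an event is serious, or is escalated, the only SAE label in its own heading contradicts the reporting section's definition of related.

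Second, a child found to be ineligible after randomisation is a conduct deviation. Nothing untoward has happened to the child. Drop-out and a change of therapist may or may not reflect harm. If these are entered as AEs, the escalation rule can convert them into SAEs by count alone.

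At stake is how the harms record can be read. In a trial that expects few SAEs, a handful of entries that are not harms could change the picture noticeably.

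**Working it through.** No figure in the article is at issue, so the main check is to compare the sections. A small calculation then shows how easily the escalation rule is reached.

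**Step 1: label against content.** The reporting section's test is whether the event resulted from a research procedure. The distress item names the therapy or assessment procedure as the cause, and the schooling/work item gives time in therapy or assessments as its example. Both describe events that can meet the test. The heading offers two places for them: plain AE, or SAE not directly related. It has no place for one that is serious and related. The first list has no item worded as caused by the procedures, so it does not supply one explicitly.

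**Step 2: content against definition.** An SAE must be an untoward medical occurrence with a serious outcome. An eligibility breach is neither. Its note describes how a deviation is handled (log it, keep the child in the intention-to-treat sample) but does not say which log. The bracket on drop-out and change of therapist treats them as occasions to look for an AE, while their place in the list makes them events. The text does not choose.

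**Step 3: content against the escalation rule.** The rule applies to any AE and exempts no listed item. If eligibility breaches count as AEs, the fourth in the study is treated as an SAE.

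**Step 4: how soon that happens.** Inputs: N = 418 and N = 560 (Sample size {14}) and the threshold of more than three reports, that is, four or more (reporting section). The per-participant rate p is assumed, because the article gives none.

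Four breaches are 4/418 = 0.96% of the smaller sample and 4/560 = 0.71% of the larger.

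With independent participants and at most one report each,

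P(X ≥ 4) = 1 − Σ (k = 0 to 3) C(N, k) p^k (1 − p)^(N−k)

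| Assumed p | Expected number, N = 418 | P(X ≥ 4), N = 418 | Expected number, N = 560 | P(X ≥ 4), N = 560 |
|---|---|---|---|---|
| 0.5% | 2.1 | 0.16 | 2.8 | 0.31 |
| 1% | 4.2 | 0.60 | 5.6 | 0.81 |
| 2% | 8.4 | 0.97 | 11.2 | >0.99 |
| 5% | 20.9 | >0.99 | 28.0 | >0.99 |

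An item affecting about 1 child in 100 is more likely than not to cross the threshold. One affecting 2 in 100 almost certainly does.

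**The case against.** The strongest reply is that the heading also covers plain AEs, and that the distress and schooling items read naturally as belonging there. Seriousness is defined for any untoward occurrence, whichever list it is in. Severe consequences such as psychiatric admission, suicidal behaviour or sustained deterioration are in the first list, which has no relatedness label. This stands in part: the text does not say that therapy-induced distress is an unrelated SAE. It does not remove the difficulty, because the escalation rule can turn a repeated AE of this kind into an SAE, and the only SAE category in its heading is then the wrong one.

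Three stronger readings are tempting, and the documents do not support them.

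- *Related harms will go unreported to the REC.* Reporting turns on the Chief Investigator's opinion of each event and also requires the event to be unexpected. The reporting section does not refer to the second list, and escalation moves recurrent distress towards the SAE route. The label creates a risk of misclassification, not a missed report.
- *Drop-outs are AEs and will swamp the total.* The bracket can equally mean that drop-out prompts a check for AEs. Withdrawals are in any case logged separately with reasons (Criteria for discontinuing or modifying allocated interventions {11b}). Any large count needs both an assumed drop-out rate and the less natural reading.
- *Drop-out will be recorded unevenly by arm.* The remark "in the C-TAU arm where there is no set end point to the treatment" explains how long economic logs are collected. It does not say that stopping cannot be recognised in usual care. The per-protocol definition applies one session minimum to both arms, and therapists in both arms report AEs.

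It is also fair to say that the article sets no AE total or between-arm AE comparison, and that tabulation may be left to the analysis plan. But the list, the label and the escalation rule are printed here, and they determine what any tabulation would contain.

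**Conclusion.** The point holds in a limited form. The second list's heading conflicts with the reporting section's definition of related for events attributed to therapy or assessment, and risks pre-labelling them if they are or become serious. The list also includes eligibility breaches, which are not untoward occurrences, and is unclear about drop-out and change of therapist. Read literally with the escalation rule, more than three such entries would be treated as an SAE, so AE and SAE counts may be diluted by events that are not harms.

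The amount of dilution cannot be stated from the article. The probabilities above rest on assumed rates, on independence between participants, and on listed items being entered as AEs. It would go too far to say that AE totals do not measure harm. The primary efficacy analysis is untouched, since ineligible children stay in the intention-to-treat sample either way.

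**What to change.** Reconcile the SAE definition, the second list and the reporting procedures as follows.

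1. Retitle the second list as potential adverse events, with no statement about relatedness.
2. State that, for every event in either list, seriousness follows the SAE definition and relatedness is judged case by case under the reporting procedures.
3. Move eligibility breaches to a protocol-deviation log, outside the AE/SAE count and the escalation rule.
4. State that drop-out or a request to change therapist prompts an AE enquiry in both arms, and counts as an AE only if an untoward event is found. Report deviations and drop-outs separately by arm.

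The cost is a change of wording in these sections and on the AE form. No new outcome measure is needed. The reported AE/SAE count may become smaller. Entries already logged under the present wording would need to be reclassified once, before analysis.

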#### Exploratory measures and objectives

*Exploratory measures:* The following measures are built in to OSI to assess parent-reported child anxiety symptoms (RCADS-P; SCAS-8P), interference (CAIS-P), global (ORS) and goal-based (GBOs) outcomes, and parent experience of the intervention (SRS), during weeks 1–7 of OSI treatment (modules 0–6) to explore the trajectory of change reported within the OSI arm.

*Exploratory objective*: To monitor child outcomes on a session-by-session basis within the novel treatment arm.

*Treatment experience:* We will conduct qualitative interviews with parents and therapists/supervisors between 14 and 26 weeks post-randomisation, and also use a therapist ‘experience of treatment’ questionnaire, measured at the end of treatment.

*Objectives:* To understand therapist and parents’ experiences of treating child anxiety problems in the current context.

*Use of the online intervention:* OSI incorporates routine outcome measures that are used for clinical purposes, but are also available to the research team through the OSI researcher portal in pseudo-anonymised form. Usage data are also available through the OSI researcher portal that provides detailed information on parents’ use of the website: frequency of sessions on the website, time spent on the website, and also time spent on the different activities.

*Objectives:* This information will be used to describe the use of and compliance with the intervention.

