### Participant timeline {13}

Where parents and their children provide online consent or assent, respectively, they will be asked to complete online baseline assessments (all questionnaires), prior to randomisation. After randomisation, parents will be asked to complete a further short questionnaire about treatment expectations and acceptability. Treatment in both arms will be organised by the clinical teams who will be requested to start as soon as possible and at most within 12 weeks of randomisation. Families allocated to the intervention arm will access OSI and a member of the clinical team will provide support as they work through each OSI module. Participating parents and children in both arms (OSI+therapist support and C-TAU) will be sent a link to complete post-treatment and follow-up assessments (questionnaires) online 14 and 26 weeks after randomisation.

Therapists will provide information on COVID-19 treatment as usual for each participant at the start of their treatment within the therapist treatment logs in order for us to be able to describe what services are delivered in the COVID-19 context, specifically the treatment approach being followed, who they are having contact with (e.g. child, parent, both), and for how long.

Therapists will provide brief demographic information at the study outset, will record information on activity with each participating family, and will complete a brief questionnaire about their experience of the treatment after completing treatment with each participating family.

We will also conduct qualitative interviews with a subgroup of parents and therapists/supervisors (*n*= 25–40), between 14 and 26 weeks after randomisation, purposively sampled on the basis of demographics, and we will continue to sample to ensure variability in treatment outcomes across both arms, if possible, to explore and to understand therapist and parents’ experiences of treating child anxiety in this context.

SPIRIT schedule of enrolment, interventions, and assessments

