#### Adverse events reporting opportunity

Trial therapists will be asked to report any adverse events that they become aware of while working with families in either arm over the whole treatment period. We will also provide parents and children an opportunity to describe any negative impacts of participating in the study after completing the questionnaires at 14 and 26 weeks and, for participating parents, after completing the qualitative interview. So as not to ‘lead’ answers, we will enquire about both the positive and negative consequences of taking part in the treatment. The research team will regularly review responses to identify any responses that indicate the presence of an adverse event.

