#### Measures routinely used to monitor outcomes in OSI

For the OSI+therapist support arm only, the OSI platform collects routine outcome measures and these will be used to help therapists to evaluate the progress of participants through treatment and to explore the trajectory of participant improvement across the course of treatment. The OSI platform routinely collects the CAIS-P, RCADS-p, SCAS-P8, and ORS as described above, and session rating scales and goal-based outcomes as described below:

Session Rating Scales (SRS): The SRS [42] assesses key dimensions of an effective therapeutic relationship and will be made available for completion at the end of each therapy session to get feedback from the parents so that any issues related to therapeutic alliances can be immediately identified and addressed within treatment. The SRS comprises four simple rating scales in which the parent rates their experience of the treatment session (with regard to relationship with the therapist, goals and topics, approach or method, and an overall rating). It uses the same visual analogue scale as the ORS. It has well-established reliability and validity [42, 43].

Goal-based outcomes (GBOs): This is a simple rating scale in which the parent rates on an 11-point scale (0–10) the extent to which their child has made progress towards up to three treatment goals [44]. Although this measure is now widely used in CAMHS (as part of the CYP IAPT initiative), its psychometric properties have not yet been established.

Routinely collected sessional measures will be used to explore the trajectory of change within the OSI+therapist support arm only to inform future developments of the programme. We will not be collecting routine outcome measures from the treatment as usual arm for comparative purposes as these will vary according to site-specific practice and treatment-specific requirements.

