While all main trial data will be directly entered into electronic Case Report Forms (eCRFs), paper versions will be provided if access to the online CRF is not possible. In this case, the original copy of the CRF will be returned to the study team and a copy will be held at the research site. All CRFs (electronic or paper) will be date stamped upon receipt. A full pre-entry review and electronic data validation for all data entered into the clinical database will be provided by study-specific programmed checks (see Data Management and Checks section below). All paper data will be locked in secure cabinets and only the researchers will have access to the files. A separate database will be used to securely store all identifiable patient information required to contact patients and permit follow-up. Access to this information will be strictly on a need-to-know basis and databases will be password protected on a secure server.

Routine sessional treatment data will be captured within OSI (for the OSI+therapist support arm only) and this will be available to the research team in pseudo-anonymised form via the OSI researcher portal. The pseudo-anonymised data will be regularly exported from OSI in CSV form and saved on the study-restricted access OneDrive for merging (by study ID) with the main trial data at the point of statistical analysis. The OSI online platform is based in the European Economic Area and is compliant with NHS digital’s requirements for data and security. As noted above, OSI will be subject to a University of Oxford TPSA and will be required to comply with recommendations.

Qualitative interviews will be audio recorded using an encrypted digital audio recorder. Recordings will be held temporarily on these audio-recording devices for no more than 24 h before being securely transferred to a restricted access folder on the University of Oxford IT Network where they will be stored separately from all other research data in a restricted access OneDrive folder. The audio recording will be either (i) transcribed by a member of the research team (manually or using Teams) or (ii) sent securely via OneDrive to a transcriber with a contract with the university (and who has been subject to and found to comply with recommendations from a TPSA). The transcriber will be required to delete all audio files after returning the verbatim transcription to the research team.

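### One adverse event criterion draws on any outcome measure in the study, but sessional measures are collected only in OSI, so this event can be ascertained more often in that arm

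*Protocol article*

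**What the plan says.** The protocol article, in its section on potential SAEs not directly related to the trial and AEs, includes this item: "A sustained and significant increase in detrimental behaviours (e.g. safety-seeking behaviours) as determined by any of the outcome measures collected throughout the study". It gives no threshold and does not say which measures qualify.

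Two sets of outcome measures exist after randomisation.

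- **Both arms.** Under Participant timeline {13}, parents and children in both arms "will be sent a link to complete post-treatment and follow-up assessments (questionnaires) online 14 and 26 weeks after randomisation".
- **OSI only.** Under Measures routinely used to monitor outcomes in OSI: "For the OSI+therapist support arm only, the OSI platform collects routine outcome measures". The scales are CAIS-P, RCADS-P, SCAS-P-8, ORS, SRS and goal-based outcomes. Exploratory measures and objectives places them "during weeks 1–7 of OSI treatment (modules 0–6) to explore the trajectory of change reported within the OSI arm", and the SPIRIT schedule lists them among the assessments as belonging to that arm alone. For the comparator the text is explicit: "We will not be collecting routine outcome measures from the treatment as usual arm for comparative purposes".

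Of the sessional scores the article says "these will be used to help therapists to evaluate the progress of participants through treatment". Under Adverse events reporting opportunity, therapists are asked to "report any adverse events that they become aware of while working with families in either arm over the whole treatment period".

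Under Reporting procedures for adverse events/serious adverse events, an AE reported more than once for one participant, or more than three times in the study, is handled as an SAE.

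**The concern.** An event that a score can establish will be found more readily where scores are taken more often. The criterion covers every outcome measure in the study, and the sessional scales are study outcome measures that exist in one arm only. The person who sees those scores, the OSI therapist, is also one of the named reporters of adverse events.

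A table of adverse events by arm could then show more of these events in OSI with no difference in true harm. Equally, a real excess in OSI could be put down to closer measurement, because nothing in the record would separate the two explanations. The repeat rule could move the imbalance from AE counts into SAE counts. The trial is open-label for families and the research team, and no separate data monitoring committee is formed by default, so the trial's own tabulation carries much of the weight on harms.

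**Working it through.** The document states no adverse event rate and no worsening rule, so there is no figure of its own to reproduce on this point. What can be counted is opportunity to measure.

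**Step 1: occasions after baseline, per child.**

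- OSI: up to 7 sessional (modules 0 to 6) + 2 scheduled (weeks 14 and 26) = up to 9.
- C-TAU: 2 scheduled.
- Ratio: 9 / 2 = 4.5.

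Seven is a maximum, since the article does not say that every scale is completed at every session.

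**Step 2: pairs of consecutive occasions**, if sustained is read as two in a row. That reading is an assumption; the document does not define the word.

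- OSI: 9 − 1 = 8 pairs.
- C-TAU: 2 − 1 = 1 pair, weeks 14 and 26.

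**Step 3: what that opportunity could do at equal true risk.** Everything in this step is assumed. Each occasion has the same probability q of a flag in both arms, with q from 2% to 10%. Scores within a child share a normal latent value with correlation r from 0 to 0.9. All sessional scores are used to identify the event. Given the child's latent value u, the flag probability is p(u) = Φ((√r·u − z₁₋q)/√(1−r)). Averaging over u:

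- flag on any occasion, k occasions: 1 − E[(1−p)^k], with k = 9 or 2;
- flag on two consecutive occasions: E[p²] in C-TAU, and 1 − E[probability of no two adjacent flags in 9] in OSI.

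| q | r | Any occasion, OSI v C-TAU (ratio) | Two consecutive, OSI v C-TAU (ratio) |
|---|---|---|---|
| 2% | 0 | 16.6% v 4.0% (4.2) | 0.31% v 0.04% (7.9) |
| 2% | 0.9 | 5.1% v 2.8% (1.8) | 2.4% v 1.2% (2.1) |
| 5% | 0.7 | 17.7% v 8.0% (2.2) | 6.0% v 2.0% (3.1) |
| 10% | 0 | 61.3% v 19.0% (3.2) | 7.2% v 1.0% (7.2) |
| 10% | 0.9 | 20.1% v 13.1% (1.5) | 12.1% v 6.9% (1.8) |

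Hand check of the first row: 1 − 0.98⁹ = 0.166 and 1 − 0.98² = 0.040. For two consecutive, 0.02² = 0.0004 in C-TAU, and about 0.02² + 7 × 0.02² × 0.98 = 0.0031 in OSI.

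Across the grid the ratio runs from 1.5 to 4.2 for any occasion and from 1.8 to 7.9 for two consecutive. Stronger correlation within a child pulls it down.

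**Step 4: the lower end.** If sessional scores play no part in identifying adverse events, both arms have 2 occasions and the ratio is 1.0. The same holds once the comparison is limited to weeks 14 and 26.

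**The case against.** The other side has a good deal of force.

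- **The criterion is narrower than deterioration.** It concerns detrimental behaviours such as safety-seeking. The sessional scales are described as covering symptoms, interference, functioning, goals and the session itself, so they reach such behaviours only indirectly. Deterioration of a pre-existing condition is a separate item, under potential SAEs, and is judged in clinical supervision. This stands.
- **It is an item on a non-exhaustive list of potential events**, with no score threshold and no automatic flag. This stands, and it is why no rate can be calculated.
- **No text says that sessional scores are screened for adverse events.** The article links routinely collected adverse event information to the 14- and 26-week questionnaires, and the research team's export of OSI data is "for merging (by study ID) with the main trial data at the point of statistical analysis". This stands for the research team. It does not close the therapist route, because the therapist sees the scores during treatment and is asked to report.
- **C-TAU is not without scores.** The article gives variation by site and treatment as its reason for not collecting routine measures there, and says under Symptoms of child anxiety that the RCADS is in routine CAMHS use. C-TAU therapists may therefore see local scores. C-TAU treatment also has no set end point (Health economic measures, on therapist logs), so the therapist-report window may be longer there. Both could offset the imbalance by an unknown amount.
- **Tabulation belongs to the statistical analysis plan**, which is not shown. That is true of tables, but the definition is fixed here, and no plan can split events by source if the source was never recorded.

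A reader might infer that the event must be found far more often in OSI by construction, or might take 8 pairs at an assumed 2% each to get 1 − 0.98⁸ = 14.9% against 2%. The documents support neither. The 2% has no source, and adjacent pairs share an observation and come from the same child, so they are not independent.

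**Conclusion.** The point holds in a limited form. As written, the criterion is open to measures that the trial collects in one arm only, with up to 9 post-baseline occasions in OSI against 2 in C-TAU, and the OSI therapists who see the extra scores also report adverse events. Ascertainment of this event can therefore be unequal at equal true risk, and the repeat rule could carry that into SAE counts.

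The size is not known. The ratios above rest on assumed flag rates, an assumed correlation, equal flagging in both arms and full use of sessional scores. The imbalance may be nil if those scores are not used for adverse events, and local measures or a longer reporting window in C-TAU may reduce it. The document does not show that an excess in OSI will occur, only that its rule allows one and would leave it uninterpretable.

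**What to change.** Add to the adverse event section, and carry into the analysis:

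1. Record the source of detection for each adverse event: therapist report, with or without an OSI sessional score; 14- or 26-week questionnaire; parent or child self-report; interview.
2. Base any between-arm comparison of this score-determined event on the 14- and 26-week measures that both arms complete.
3. Report events detected through OSI sessional scores in full, by arm and source, but separately from that comparison. Show in the same way any SAE that arises from the repeat rule.

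Individual safety follow-up and logging stay as they are.

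The cost is a short addition to the text and one extra field on the AE form. The article gives 03/08/2022 as the end of recruitment; for events already logged, the source can be classified when they are reviewed before analysis, as far as the records allow. The downside is fewer events in the comparative count, and so less precision on this item.
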